## Abstract

**Background:**

The optimal form of exercise for individuals with cancer has yet to be identified, but there is evidence that exercise improves their quality of life. The aim of this study is to assess the efficacy and efficiency of an innovative physical exercise programme, for individuals undergoing chemotherapy for breast, gastrointestinal or non-small cell lung tumours, for improving quality of life, reducing level of fatigue, and enhancing functional capacity over time.

**Design/Methods:**

We will conduct a clinical trial in 66 patients with stage IV breast, gastrointestinal or non-small cell lung cancer, recruited by the Department of Oncology of the referral hospital from 4 primary care health centres of the Basque Health Service (Osakidetza). These patients will be randomised to one of two groups. The treatment common to both groups will be the usual care for cancer: optimized usual drug therapies and strengthening of self-care; in addition, patients in the intervention group will participate in a 2-month exercise programme, including both aerobic and strength exercises, supervised by nurses in their health centre. The principal outcome variable is health-related quality of life, measured blindly with the 30-item European Organization for the Research and Treatment of Cancer Core Quality of Life Questionnaire and Short Form-36 four times: at baseline, and 2, 6 and 12 months later. The secondary outcome variables are fatigue (Functional Assessment of Chronic Illness Therapy-Fatigue questionnaire), functional capacity (6-Minute Walk Test and cardiorespiratory test), muscle strength (hand-held dynamometry and sit-to-stand test), radiological response to treatment (Response Evaluation Criteria In Solid Tumors) and progression-free and overall survival. Age, sex, diagnosis, chemotherapy regimen, Eastern Cooperative Oncology Group performance status and smoking status will be considered as predictive variables. Data will be analysed on an intention-to-treat basis, comparing changes at each time point between groups, adjusting for baseline values by analysis of covariance.

**Discussion:**

As well as achieving the objectives set, this study will provide us with information on patient perception of the care received and an opportunity to develop a project based on collaborative action between the primary care and oncology professionals.

**Trial registration:**

ClinicalTrials.gov Identifier: NCT01786122 Registration date: 02/05/2013.

## Background

Cancer is the second most common cause of death in industrialised countries [1]. In the coming decades, it is expected to become the first cause of morbidity and mortality across the world and it already is in the Basque Country. In 2008, there were 12.7 million new cases of cancer worldwide, the most common type being lung cancer, followed by breast and colorectal cancers. It is estimated that the worldwide incidence of cancer will reach 21 million new cases by 2030 [2,3].

At the same time, great advances in the survival of cancer patients highlight the need to keep their quality of life as high as possible [4]. Hence, though for many years survival has been the most important factor in treatment selection, increasing importance is given to patient quality of life and complementary therapies are used to combine the promotion of physical wellness with meeting holistic and psychosocial needs [5-7]. Physical exercise has become the cornerstone of this approach in many diseases [8], and it is plausible that it may help mitigate some of the adverse effects of treatments in cancer: decreasing fatigue, increasing cardiorespiratory fitness and physical condition, and strengthening the immune system, and together with these, reducing recurrence rates, extending survival and improving quality of life [4,5,8-12]. Nevertheless, researchers have only recently started to study its effect in cancer patients [9].

The physical and psychosocial functioning of cancer patients is impaired by the disease itself and the toxicity of treatments [13], and in parallel their quality of life deteriorates [14,15]. They become increasingly easily fatigued, loose muscle mass and have generalised muscle weakness as well as lower exercise tolerance [13,16]. Consequently, patients enter a vicious circle of progressively increasing fatigue, dyspnoea and declining functional capacity to perform activities of daily living [17,18].

On the basis of research to date, we can hypothesise that physical exercise has a positive effect on quality of life, improves physical condition and reduces fatigue in cancer patients [11,19-23]. However, the scientific evidence available is still limited, few studies having been conducted and participants in these studies not being representative of all cancer patients. The studies have been small, sometimes without suitable control groups and, to date, have focused on the survival phase, in which palliative care is the main priority, rather than the treatment phase. Nevertheless, some studies have found that patients who exercise during the treatment phase improve their functional capacity and experience less emotional distress and fatigue [24-28]. On the other hand, it is not yet clear what would be the optimal structure for an exercise programme, in terms of type, duration, frequency and intensity, to improve quality of life in cancer patients [29-33]. It seems that the combination of aerobic exercise and strength training improves muscle function, reduces fatigue and improves quality of life during treatment [34-36]. Nevertheless, more studies are required to demonstrate that cardiovascular training combined with strength training is beneficial for patients diagnosed with cancer at all stages of the disease.

## Aim

To assess the efficacy and efficiency of an innovative physical exercise programme, for people under chemotherapy for cancer (breast, gastrointestinal and non-small cell lung cancers), for improving quality of life, reducing level of fatigue, and enhancing functional capacity, compared to usual care alone.

### Primary objectives

- To measure changes in health-related quality of life (HRQOL) between baseline and 2 months in intervention and control groups, assessing the difference in HRQOL between the groups, which is attributable to exercise.

### Secondary objectives

- To measure changes in functional capacity and level of fatigue in the intervention and control groups, assessing differences between the groups, which are attributable to exercise.

- To explore whether effects attributable to the intervention vary between subgroups of participants as a function of age, sex, cancer stage, histological findings, radiotherapy or chemotherapy regimens, as well as whether any of these variables play a role as confounders.

- To investigate whether any differences observed at 2 months are maintained in the longer term, in particular, at 6 and 12 months.

## Methods/design

### Study design

This is a parallel-group randomised controlled clinical trial in patients with breast, gastrointestinal or non-small cell lung cancer at stage IV of the disease. The treatment common to both groups will be the usual care for cancer, namely, optimized usual drug therapies and strengthening of self-care. The intervention group will also receive an intervention based on a supervised exercise programme led by nurses combined with education on healthy living. The patients included in the study will pass through two successive phases: a “treatment optimization phase” and a “phase for follow-up and assessment of results”. Patients are to be followed-up for 1 year, with four blind assessments: at baseline, and 2, 6 and 12 months later (Figure 1).

**Figure 1 Fig1:**
[figure not shown]
**Study flowchart.**

### Study setting

The Department of Oncology at Cruces University Hospital will recruit patients from four primary care health centres of the Basque Health Service (Osakidetza).

Each health centre has a well-established infrastructure including:A laboratory for measuring physical condition with cycle ergometers, treadmill ergometers, weights, dumbbells, dynamometers, pulse oximeters, electrocardiographs, anthropometric measuring instruments, blood gas analysers, and heart rate monitors, as well as defibrillators and systems for data management, among other equipment.Shared databases.Integrated data management systems based on a private virtual network connecting all the collaborating centres.

As the centre coordinating the study and provider of methodological support, the Primary Care Research Unit has:A license for the SAS software to perform all the statistical analyses.Information technology facilities, as well as premises for carrying out training activities and coordination meetings.Technical secretarial support.

### Study population

#### Inclusion criteria

Age of 18–70 years old.Histologically confirmed diagnosis of stage IV breast, gastrointestinal or non-small cell lung cancer and an Eastern Cooperative Oncology Group (ECOG) performance status (PS) of 0 or 1.Usual first line chemotherapy treatment for the type of cancer in question.Adequate renal and liver function and blood parameters.

#### Exclusion criteria

Brain metastases.High risk of fracture (bone metastasis).Decompensated heart disease, uncontrolled hypertension (systolic blood pressure >200 or diastolic blood pressure >110 mm Hg), heart failure (New York Heart Association Class II or greater), or constrictive pericarditis.Other health problems in which physical exercise is contraindicated, at the discretion of the researchers.Regular physical activity (150 min of moderate or 75 min of vigorous physical activity/week).

### Recruitment

For recruiting patients, the hospital’s Department of Oncology will establish a system for identifying patients discharged with stage IV breast, gastrointestinal or non-small cell lung cancers. The oncologists will tell patients about the study, invite them to participate and give them a written informed consent form, as well as informing the doctor in charge of the study in the patients’ health centre. Patients who agree to participate will be included in the study once they have signed the informed consent form and baseline data have been collected. They will be invited to an inclusion visit at which a nurse will carry out this baseline assessment and record the data.

### Randomisation

Randomization will be performed centrally, by phoning the Primary Care Research Unit, once baseline measurements have been taken at the health centres. Individuals independent of the organisation responsible for the study management and researchers will randomize patients using a computer-based random number generator. Patients will be registered and allocated on a 1:1 basis to one of the two study arms.

### Protocol for the control group

Patients in the control group will all receive the usual treatment for the type of cancer they have been diagnosed with (e.g., platinum-based chemotherapy for non-small cell lung cancer), following standard oncological criteria. They will be assessed before, during and after chemotherapy in accordance with the established protocol.

### Protocol for the intervention group

The intervention group treatment differs from that of the controls in that, in addition to the usual care, they will participate in a programme based on continuous and moderate-intensity interval aerobic exercise combined with exercises for muscle strength and joint mobility. The aerobic exercise will be performed on a cycle ergometer, this system being more suitable than treadmill exercise for cancer patients, as adverse effects of their pharmacological treatment may cause them to have difficulty with activities requiring balance and coordination. The exercise programme takes into account the principles of progression and individualization, as well precautions regarding exercise by cancer patients.

#### Phase 1 (8 weeks, 3 sessions/week)

For the first 2 months, patients will follow a progressive exercise programme consisting of 24 sessions, the intensity being lower at the beginning and increasing in the second month (Figure 2). Two of the sessions each week will take place under the supervision of the nurse in the laboratory, while the third session is to be carried out independently in the area around the health centre, with the aim of promoting patient independence, and for this, patients are to wear a heart rate monitor pre-programmed by the nurse. Each laboratory session will include health education, as well as aerobic exercise and muscle strength exercises.

**Figure 2 Fig2:**
[figure not shown]
**Exercise programme of the intervention group.**

#### Education on healthy living

Patients will receive advice on the type of exercise to do independently and be taught how to measure their heart rate and to use the heart rate monitor with heart rate alerts.

#### Aerobic exercise

In each session, the intensity of the exercise is adapted to the physical condition of patient. The activity will be monitored using the Borg scale to rate the patient’s perceived exertion before and after each session and by watching for the appearance of symptoms. During the first month, patients will perform continuous aerobic exercise at a constant intensity equivalent to 60-70% of their heart rate reserve (HRR). In the second month, the intensity of the exercise will be increased, patients performing aerobic interval exercise, alternating 5-minute periods of very high intensity at 75-90% of their HRR with 2-minute periods of active resting at 40% of their HRR. This aerobic exercise is to be carried out before strength exercises to ensure cardiovascular and muscular warm-up.

#### Strength and joint mobility exercises

In each session, patients will carry out 8 exercises each with 2 series of 8–12 repetitions. In this way, the muscles involved in activities of daily living will be exercised (biceps, triceps, deltoid and trapezius muscles; knee and hip extensors and flexors; and deep abdominal and back muscles related to posture), applying a different weight for each muscle group. Dumbbells and exercise resistance bands will be used for upper limbs and lower limbs, respectively.

At the end of the supervised exercise, to assess the acceptance of this type of intervention, the nurse will interview patients about their experience of the programme. This interview will be audio recorded and later analysed by a sociologist experienced in qualitative analysis.

#### Phase II

It is envisaged that the training received in Phase I will help patients to maintain an exercise routine. They will be trained to carry out an exercise programme similar to that of the intervention, independently and indefinitely, using community facilities.

### Outcome measures

#### Primary outcome measure

Changes in HRQOL after 2 months to assess the results of Phase I. HRQOL will be measured blindly using the 30-item European Organization for the Research and Treatment of Cancer Core Quality of Life Questionnaire (EORTC QLQ-C30). This questionnaire is specific for assessing HRQOL of patients with cancer, asking how they have been feeling in the previous 7 days. The 30 items cover 9 multi-item scales: 5 functional scales (physical, role, cognitive, emotional and social functioning) and 3 symptom scales (fatigue, pain, and nausea/vomiting), as well as a global health status and quality of life scale. It also contains ratings of certain symptoms (dyspnoea, insomnia, appetite loss, constipation and diarrhoea). The raw scores are linearly transformed to standard scores between 0 and 100. This questionnaire has been considered valid and reliable in multiple studies on cancer patients. In addition, we will use the Short Form-36 (SF-36) generic quality of life questionnaire. Both questionnaires have been validated for the Spanish population [37,38].

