### Sample size

We estimate that we need to analyse 26 patients per group to detect a difference of 20 points in the global scales and subscales of the EORTC QLQ-C30 as significant, a difference considered to be important from the patient point of view (level of significance, 0.05; power, 0.80 and standard deviation, 25). For this reason, we will include 33 patients per group, that is, a total of 66, allowing for a loss to follow-up of 20%. Given that in the pilot 66% of candidates signed the informed consent form, we need to invite a total of 100 patients to participate.

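### No single QLQ-C30 score is named as the primary endpoint, while the sample size applies one unshared 0.05 to the global scales and subscales together

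*Protocol article*

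**What the plan says.** Under Primary outcome measure, the protocol article gives the endpoint as "Changes in HRQOL after 2 months to assess the results of Phase I", measured with the QLQ-C30. The instrument is then described: "The 30 items cover 9 multi-item scales: 5 functional scales (physical, role, cognitive, emotional and social functioning) and 3 symptom scales", with a global health status and quality of life scale as the ninth. The text continues: "It also contains ratings of certain symptoms (dyspnoea, insomnia, appetite loss, constipation and diarrhoea". A second instrument follows under the same heading: "In addition, we will use the Short Form-36 (SF-36) generic quality of life questionnaire". Neither the SF-36 nor any QLQ-C30 scale appears under Secondary outcome measures.

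The Sample size section plans 26 analysed patients per group to "detect a difference of 20 points in the global scales and subscales of the EORTC QLQ-C30 as significant", at significance level 0.05, power 0.80 and standard deviation 25. The Limitations section again speaks of the global scale and subscales together.

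The abstract gives the principal outcome variable as quality of life measured with both questionnaires: "Core Quality of Life Questionnaire and Short Form-36 four times: at baseline, and 2, 6 and 12 months later".

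The time point is settled. The primary objective is "To measure changes in health-related quality of life (HRQOL) between baseline and 2 months in intervention and control groups", and the 6- and 12-month comparisons are a secondary objective. The Statistical analysis section refers to the primary outcome variable in the singular, without saying which score it is, and plans baseline-adjusted ANCOVA with 95% confidence intervals.

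**The concern.** The document fixes an instrument and a time point but not a variable. The QLQ-C30, as described here, yields nine multi-item scales and five single symptom ratings, and the sample size is written as if one 0.05-level calculation served the global scale and the subscales alike. A reader of the results could not tell from this text which comparison decides the trial.

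Two properties are at stake. If several scales can each support the claim that exercise improves quality of life, 0.05 is not the error rate of that claim. If the 0.05 is shared among them, the 80% power is no longer what the calculation delivers. There is also an overlap: fatigue is a secondary objective with its own questionnaire, yet the QLQ-C30 fatigue scale lies inside the primary outcome, so a benefit on fatigue alone could be reported at either level.

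**Working it through.** **Inputs.** From Sample size: difference 20, SD 25, significance level 0.05, power 0.80, 26 analysed per group, 20% loss. From Primary outcome measure: 5 functional + 3 symptom + 1 global = 9 multi-item scales, and 5 single symptom ratings, so 14 scores in all. Assumed, because the document gives no values: correlation between scales 0.3 to 0.7, the same for all pairs; baseline-to-follow-up correlation 0.3 to 0.5.

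**1. The plan's own figure.** Standardised difference: 20/25 = 0.8. Normal formula: 2 × (1.960 + 0.842)² / 0.8² = 24.5, so 25 per group. The two-sample t-test version gives 25.5, so 26. Allowing for loss: 26/0.80 = 32.5, so 33 per group and 66 in total. The figures reproduce for one two-sided test at 0.05, with t-test power 0.81 at 26 per group.

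**2. Error rate if any of the 9 multi-item scales could carry the claim.**
- Either direction, independent scales: 1 − 0.95⁹ = 0.370.
- Favourable direction only, independent scales: 1 − 0.975⁹ = 0.204, against a nominal 0.025.
- With equally correlated normal test statistics:

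| Assumed correlation | Either direction | Favourable only |
|---|---|---|
| 0.3 | 0.326 | 0.165 |
| 0.5 | 0.269 | 0.135 |
| 0.7 | 0.202 | 0.101 |

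**3. Power if 0.05 is shared by Bonferroni over the 9 scales.** The level per scale is 0.05/9 = 0.00556. Power is for 20 points on a given scale at 26 per group.
- Unadjusted t-test: 0.50. Reaching 80% would take 42.8, so 43 analysed per group; 43/0.80 = 53.75, so 54 per group and 108 in total.
- ANCOVA, reading SD 25 as the SD of the follow-up score, so that the residual SD is 25 × √(1 − r²): at r = 0.3 the standardised difference is 0.8/√0.91 = 0.839 and power is 0.55; at r = 0.5 it is 0.8/√0.75 = 0.924 and power is 0.67.
- ANCOVA needs roughly 42.8 × (1 − r²) per group. Setting this equal to 26 gives r² = 1 − 26/42.8 = 0.39, so r is about 0.63. The shortfall would disappear only if the baseline correlation were at about that level or higher.

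**4. One named score.** The level stays at 0.05, and 26 analysed and 33 recruited per group stand as printed.

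**The case against.** **No rule says that any significant scale is enough.** A reader might infer that the plan, followed as written, declares success on any one scale. It does not say so: it refers to one primary outcome variable and promises estimates with confidence intervals. The error rates above are therefore conditional on that rule. What remains is that the text does not exclude it, because the single variable is never identified.

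**Fourteen or more primary tests is a stronger count than the text supports.** The list of scales and symptom ratings describes the questionnaire; it is not an endpoint list. The Sample size section does not mention the single symptom ratings, and testing them or the SF-36 at 0.05 would be an inference. The nine multi-item scales are the firmest basis, so the figures use those.

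**The SF-36 is less prominent in the body.** There it is an addition, and the sample size rests on the QLQ-C30 alone. Only the abstract puts the two on an equal footing, so this part is mainly a mismatch between abstract and body.

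**Later visits do not multiply the primary.** A reader of the abstract might take all four assessments as primary. The phrase is a measurement schedule, and the objectives fix 2 months for the primary comparison and make 6 and 12 months secondary.

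**Bonferroni is not proposed, and it is conservative for correlated scales.** This is accepted; it serves only to show the price of sharing 0.05, and ANCOVA recovers part of the loss.

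**A multiplicity method may sit in an analysis plan that is not shown.** This is also accepted, and its absence is not the point here. Which score is primary, and which score the trial is sized on, are matters this document does state, and it states them for a group of scales.

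**Conclusion.** The point holds in a limited form. The primary outcome is fixed at 2 months on the QLQ-C30, but no score is named, and a calculation valid for one two-sided test is attached to the global scales and subscales together.

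Under a rule that any of nine scales suffices, the nominal 5% becomes about 20% to 37%, and the nominal 2.5% for a false claim of benefit becomes about 10% to 20%, depending on the correlation assumed. Under Bonferroni over nine scales, the stated 80% becomes about 50% by t-test or 55% to 67% by ANCOVA, unless the baseline correlation is higher than assumed here. All of this takes the plan's SD of 25 as given. The stated 0.05 and 80% are both secured at this sample size once one score is named.

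The documents do not support the stronger statement that the trial will test fourteen or more primary scores at 0.05 each, or that its false-positive rate is any particular figure. The sample size arithmetic itself is not in error.

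**What to change.** Before any data are seen by arm, name one QLQ-C30 score at 2 months as the single primary endpoint, analysed by the planned baseline-adjusted ANCOVA at two-sided 0.05. Global health status/quality of life is one candidate; the document does not single it out, so the choice is the sponsor's. Reword the Sample size section so that 26 analysed and 33 recruited per group refer to that score only. List the other QLQ-C30 scales and the SF-36 as secondary, and align the abstract on the role of the SF-36. The 6- and 12-month comparisons are already secondary and need no change.

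The cost is wording in three sections: no more patients, no new data and no change of method. The downside is that a benefit seen only on another scale could no longer be called the primary result.
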